### Statistical analysis

Baseline comparability between CWC and SC conditions will be analysed using multiple planned comparisons for continuous measures, and chi-squared tests for categorical variables. Hypothesis testing involving assessment of differential change over time between groups will be assessed using Hierarchical Linear Mixed Modelling (HLM). This HLM statistical method presumes an intent-to-treat framework by allowing the number of observations to vary between participants and thereby effectively handles missing data. For each outcome, linear effects of time of measurement, condition, and condition-by-time interaction will be analysed. Fixed effects parameters for the time of assessment and intervention condition will be tested with the Wald test (t-test, *p* < 0.05, two-sided) and 95% confidence intervals. Cohen’s (d) effect size will be calculated for all analyses. Analyses will focus on the primary outcome (HADS) and secondary outcomes (GAD-7, CSS, SIDAS, & WHO-5) for both CWC and SC, with the main outcome time point being the 2-month follow-up, relative to baseline. To assess for potential bias from attrition, completer analyses will also be conducted using only the data on participants completing the allocated intervention as planned. Two-tailed tests will be reported with a significance level of *p* < 0.05 for all analyses.

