### Randomization

The randomization will be conducted by a computerized software on a 1:1 basis and will occur following completion of the T0 assessment. Two project managers who are independent of any other aspects of the treatment study being conducted in Bangalore, India will allocate individuals to CWC or SC groups. Following this time, individuals will be invited for the introductory online session with the group facilitator.

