### Sample size

The sample size calculation for this treatment trial was based on a two-group comparison of the primary outcome at the 2-month follow-up timepoint. In order to obtain estimates of parameters, a comparable data set from a recent treatment trial in a high-income setting was used [20]. The power analysis indicated that to achieve a moderate effect size of (0.6) a sample size of 90 participants would be needed per arm to provide power of 0.95 (alpha = 0.05, two-sided); on the expectation that there would be approximately 10% attrition at the 2-month follow-up assessment, it was estimated that a total of 200 participants would need to be enrolled into the study.

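### Read literally, the linear-time model does not deliver the T2-versus-baseline contrast that the plan makes primary; time should be categorical and the T2 contrast named

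*Protocol article*

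**What the plan says.** Design & setting describes a two-arm design crossed with four assessment points (T0 baseline, T1 post-intervention, T2 at two months, T3 at six months) and sets T2 as the primary time point. Sample size says that the calculation "was based on a two-group comparison of the primary outcome at the 2-month follow-up timepoint". Statistical analysis states that the analyses focus on HADS and the secondary outcomes "with the main outcome time point being the 2-month follow-up, relative to baseline".

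The model in that same section is a hierarchical linear mixed model: "For each outcome, linear effects of time of measurement, condition, and condition-by-time interaction will be analysed". On testing it adds: "Fixed effects parameters for the time of assessment and intervention condition will be tested with the Wald test". It does not name the interaction in that sentence, define a T2 contrast, or say how time is coded.

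**The concern.** Three statements ask a visit-specific question: how the arms differ at T2, relative to baseline. The stated model answers another one: how fast the arms diverge, on average, along a straight line through T0, T1, T2 and T3. The two agree only when the arm difference really is linear in the time scale used. Otherwise T1 and T3 feed into the primary estimate and test, and an unstated choice of time coding changes the answer for the same data. The section also promises Cohen's d for all analyses, so a distorted T2 estimate could become the reported effect size. Leaving both readings open would also allow a choice between slope and T2 contrast after the results are seen.

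**Working it through.** **1. The plan's own figure.** Effect size 0.6, two-sided alpha 0.05, power 0.95: n per arm = 2(1.960 + 1.645)² / 0.6² = 72.2, so 73 (74 with the t distribution). The plan states "a sample size of 90 participants would be needed per arm to provide power of 0.95 (alpha = 0.05, two-sided"). The 90 is not reproduced, but it errs on the safe side: at 90 per arm the power is 0.98. The enrolment step does reproduce: 180 / (1 − 0.10) = 200. This is a separate matter; 90 per arm is used below.

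**2. Inputs.** From the documents: 90 per arm, true T2 difference 0.6 SD, four visits, six weekly sessions, T2 and T3 at two and six months after treatment. Assumed, because the documents do not give them: unit SD at each visit, equal correlation ρ = 0.5 between visits, T1 at 1.5 months, and time coded either 0, 1, 2, 3 or in months 0, 1.5, 3.5, 7.5. The arm differences δ at T0 to T3 are also assumed: sustained (0, 0.6, 0.6, 0.6) or partly fading (0, 0.6, 0.6, 0.3).

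**3. Slope difference.** b = Σ(t − t̄)δ / Sxx, with SE(b) = √[2(1 − ρ) / (90 Sxx)].

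- Visit coding: t̄ = 1.5, Sxx = 5, SE = 0.0471.
- Months: t̄ = 3.125, Sxx = 31.69, SE = 0.0187.

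The implied change from T0 to T2 is b × t(T2), with t(T2) = 2 or 3.5.

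- Sustained, visits: b = 0.90 / 5 = 0.18; implied 0.36; z = 3.82.
- Sustained, months: b = 1.875 / 31.69 = 0.0592; implied 0.21; z = 3.16.
- Fading, visits: b = 0.45 / 5 = 0.09; implied 0.18; z = 1.91.
- Fading, months: b = 0.5625 / 31.69 = 0.0178; implied 0.06; z = 0.95.

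**4. Fitted arm difference at T2** (condition plus slope × time) = δ̄ + b(t(T2) − t̄).

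- Sustained: 0.45 + 0.18 × 0.5 = 0.54 (visits); 0.45 + 0.0592 × 0.375 = 0.47 (months).
- Fading: 0.375 + 0.09 × 0.5 = 0.42 (visits); 0.375 + 0.0178 × 0.375 = 0.38 (months).

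Its SE is √{(2/90)[ρ + (1 − ρ)(1/4 + (t(T2) − t̄)² / Sxx)]}, which is 0.120 (visits) or 0.118 (months).

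**5. Categorical time, T2 minus T0.** SE = √[4(1 − ρ) / 90] = 0.149; z = 0.6 / 0.149 = 4.02; power 98%, whatever happens at T1 and T3.

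| True differences T1, T2, T3 | Coding | Implied T2 change (slope-test power) | Fitted T2 difference (power) | Categorical T2 − T0 (power) |
|---|---|---|---|---|
| 0.6, 0.6, 0.6 | visits | 0.36 (97%) | 0.54 (99%) | 0.60 (98%) |
| 0.6, 0.6, 0.6 | months | 0.21 (88.5%) | 0.47 (98%) | 0.60 (98%) |
| 0.6, 0.6, 0.3 | visits | 0.18 (48%) | 0.42 (94%) | 0.60 (98%) |
| 0.6, 0.6, 0.3 | months | 0.06 (16%) | 0.38 (90%) | 0.60 (98%) |

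**6. Range.** With ρ = 0.7 the estimates do not move. Slope power becomes 99.9% or 98% (sustained) and 69% or 23% (fading), against 99.9% for the categorical contrast. If the effect fades to zero at T3, the implied T2 change is 0.00 (visits) or −0.08 (months). If the difference grows by equal steps (0.3, 0.6, 0.9), visit coding recovers 0.60 with power near 1, but coding in months gives 0.41.

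**The case against.** The strongest reply is that a T2 comparison is stated: the analysis section names the 2-month follow-up relative to baseline as its focus, and the design crosses arm with four assessment points, which suggests a four-level time factor. A T2 contrast may well be intended. That stands, and it means the text conflicts with itself; it does not settle on a slope-only test. It does not rescue the model as worded, because a T2 change taken from a linear-time model is only slope × time. Nor is this detail left to an analysis plan that is not shown: the article chose a form for time, and an analysis plan could repair it only by departing from the word linear.

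A reader might go further in four ways that the documents do not support.

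- That the primary test will miss the T2 effect. With a sustained effect the slope test keeps 97% or 88.5% power. Serious loss needs fading by T3, and nothing in the article says what trajectory to expect.
- That the T2 difference must be badly understated. The larger shortfalls belong to the implied change from baseline. The fitted T2 difference falls short by less.
- That the condition parameter is merely the baseline difference. That holds if time is zero at baseline. If time were centred at T2, the parameter would be the model's T2 difference. The coding is not stated.
- That leaving out baseline adjustment is an error. The plan declares change from baseline, which is a legitimate comparison.

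**Conclusion.** The point holds as an inconsistency in the stated analysis. The declared primary comparison is T2 relative to baseline; the stated model is linear in time, and the sentence on Wald tests names neither the interaction nor a T2 contrast. Unless the arm difference is linear in the coding used, the model as worded does not estimate what the trial was sized to detect.

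The size depends on which quantity is reported and on the course of the effect. For a true 0.60 SD, the implied T2 change lies between 0.06 and 0.36 and the fitted T2 difference between 0.38 and 0.54 across the two main scenarios and two codings. Slope-test power runs from 16% to 97% at correlation 0.5. These figures illustrate the effect of the wording under assumed correlation, coding and T1 and T3 effects; they do not predict this trial's result. The wording should be settled before unblinded analysis, because it decides which number is the primary result.

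**What to change.** State that assessment point enters the model as a four-level categorical factor, in line with the design section. For each HADS primary outcome, declare the condition difference at T2 relative to baseline as the single primary contrast, with its Wald test and confidence interval. Report the T1 and T3 differences as secondary contrasts from the same model. Bring the sentence listing the tested parameters into line with this.

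Adjusting the T2 comparison for the baseline HADS already collected is optional. Its SE would be √[2(1 − ρ²) / 90] = 0.129 instead of 0.149, which raises power from 98% to 99.6% under the same assumptions.

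The cost is a change of wording and a few more model parameters. No new data are needed. If the effect did grow linearly by visit, the slope test would be slightly more powerful (near 100% against 98%), so little is given up.

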### Interventions

*Coping with COVID* (CWC). The CWC programme is a brief psychological intervention developed to reduce symptoms of stress (e.g., depression, anxiety) for those affected by ongoing adversity. This programme was adapted to include evidence-based strategies that specifically target COVID-19 related distress in a young adult population. This includes education about common reactions to COVID-19, stress management (i.e., slow diaphragmatic breathing), problem solving, worry management, behavioural activation, skills to strengthen access to social support, and relapse prevention. CWC will be delivered over 6 weekly sessions of 60-minute duration. The programme will be delivered in anticipated group size of 4–5 participants via the Google Meet online platform.

*Supportive Counselling (SC).* The SC arm will involve 6 weekly 60-minute video-conferencing sessions that will be led by a trained peer facilitator, who will facilitate group discussions about how students are coping with the pandemic, ventilation of reactions to problems experienced, and discussion of possible solutions. Those randomised to the SC arm will not receive support relating to CWC strategies.

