### Facilitator selection, training, and supervision

The CWC and SC interventions will be conducted by trained peer facilitators, who will be male and female non-specialist providers recruited from CHRIST (Deemed to be University) campuses across India. They will receive 8 days of training in basic counselling skills, delivery of CWC and SC techniques, group facilitation and self-care. At the end of training, all facilitators will be required to conduct a practise group of both CWC and SC interventions under the close supervision of trained clinical psychologists. In the event that a practice cycle cannot be conducted, a role-play competency assessment will be conducted. To this end, both practice cycles and role-plays will be used to assess facilitator competency prior to implementation of groups for the RCT. Regular weekly supervision will be provided remotely by video teleconferencing with a clinical psychologist (DK, KD, SA, or SY) to ensure treatment adherence and provide ongoing support to facilitators.

CWC and SC groups will be conducted across two cycles from Oct 2021 to Dec 2022 such that training, practice cycles and groups sessions can be run outside of assessment and holiday periods as determined within the CHRIST (Deemed to be university) college semester schedules. Group debrief and feedback sessions will be conducted mid-way and at the end of cycle 1 implementation of sessions such that important learnings can be carried forward to cycle 2 of the RCT.

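### Treatment is delivered in small groups nested within arm, but the analysis as described has no therapy-group effect; if outcomes within groups are positively correlated, the primary test is anti-conservative

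*Protocol article*

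**What the plan says.** **Design.** The Randomization section allocates individuals: "The randomization will be conducted by a computerized software on a 1:1 basis". Under Interventions, both arms then receive six weekly 60-minute videoconference sessions led by a peer facilitator. For CWC, "The programme will be delivered in anticipated group size of 4–5 participants via the Google Meet online platform". No group size is stated for SC, but the abstract and the Aims & hypotheses section describe the trial as run in a group format. Facilitators are trained in, and practise, both interventions, and "CWC and SC groups will be conducted across two cycles from Oct 2021 to Dec 2022".

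**Analysis.** The Statistical analysis section names a hierarchical linear mixed model with effects of time, condition and condition-by-time. "Fixed effects parameters for the time of assessment and intervention condition will be tested with the Wald test", two-sided at 5%, with the 2-month visit relative to baseline as the main contrast. The only nesting it describes is a varying number of observations per participant. It lists no random effects and mentions neither therapy group nor facilitator.

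**Sample size.** The calculation "was based on a two-group comparison of the primary outcome at the 2-month follow-up timepoint". "The power analysis indicated that to achieve a moderate effect size of (0.6) a sample size of 90 participants would be needed per arm", for power 0.95 at two-sided alpha 0.05. With "approximately 10% attrition at the 2-month follow-up assessment, it was estimated that a total of 200 participants would need to be enrolled". No ICC, group size or design effect appears.

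**The concern.** Members of one therapy group share a facilitator, a discussion and each other for six weeks. Their later outcomes may therefore resemble one another more than those of people in different groups. Because each group sits wholly within one arm, this shared component does not cancel in the comparison of arms; it adds to the variance of the arm difference. A model that knows only about repeated measures on participants leaves that variance out.

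The matter is close to the trial's question. The Background asks whether gains come from the taught strategies or from non-specific elements such as attention and group involvement. Variation between groups is part of what must be separated from the effect of CWC content. If it is ignored, intervals are too narrow and a finding of superiority is easier to reach by chance than the stated 5% implies.

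**Working it through.** **Inputs from the protocol:** effect size 0.6; power 0.95; two-sided alpha 0.05; 90 per arm; 10% attrition; CWC group size m = 4–5.

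**Assumed:** the same m in SC, and an ICC of 0.01 to 0.10, since the protocol gives none. With 90 analysed per arm there are about 18 (90/5) to 22 (90/4) groups per arm.

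**1. The plan's own sample size.** n per arm = 2(1.960 + 1.645)²/0.6² = 72.2, so 73 (73.2, so 74, with the t distribution). The stated 90 is not reproduced; at d = 0.6 it gives power of about 0.98. The attrition step does reproduce: 90/0.9 = 100 per arm, 200 in total.

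**2. Type I error for a comparison at 2 months that ignores groups.** Design effect DE = 1 + (m − 1)·ICC. The true standard error is √DE times the reported one. Actual alpha = 2[1 − Φ(1.96/√DE)].

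| ICC (assumed) | DE, m = 4 to 5 | √DE | Actual alpha, formula | Simulated |
|---|---|---|---|---|
| 0 | 1.00 | 1.00 | 5.0% | 4.8–5.0% |
| 0.01 | 1.03–1.04 | 1.01–1.02 | 5.4–5.5% | 5.5% |
| 0.05 | 1.15–1.20 | 1.07–1.10 | 6.8–7.4% | 7.1–7.3% |
| 0.10 | 1.30–1.40 | 1.14–1.18 | 8.6–9.8% | 9.0–9.8% |

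The simulation used 40,000 null trials per setting, with 90 per arm in groups of 5 or of alternating 4 and 5, analysed by a t-test that ignores groups.

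**3. Carry-over to change from baseline.** Groups form after the T0 assessment, so take the group effect as absent at T0 and present at T2. With equal variances and baseline-to-T2 correlation r, the change score has variance proportional to 2(1 − r), and its ICC is ICC/[2(1 − r)]. With m = 4.5 and a T2 ICC of 0.05:

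- r = 0.3: 0.05/1.4 = 0.036, DE 1.125, alpha 6.5%
- r = 0.5: 0.05/1.0 = 0.050, DE 1.175, alpha 7.1%
- r = 0.7: 0.05/0.6 = 0.083, DE 1.292, alpha 8.5%

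The protocol gives no r, so these values are illustrative. A simulation of the change contrast at r = 0.5 (20,000 null trials, 20 groups of 4–5 per arm) gave 7.2% at ICC 0.05 and 9.1% at ICC 0.10 when groups were ignored. With group means as the unit it gave 5.1% and 5.2%.

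**4. Why a time-constant group intercept is not enough.** Such a term adds the same quantity to a member's T0 and T2 values, so it drops out of T2 minus T0. The standard error of the condition-by-time contrast would not reflect a group effect that arises after baseline.

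**5. Power at d = 0.6, 90 analysed per arm, clustering allowed for** (effective n = 90/DE):

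- No clustering: 0.98
- ICC 0.05: 0.957–0.964
- ICC 0.10: 0.925–0.942

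The surplus 90/73 = 1.23 covers a design effect up to an ICC of (1.233 − 1)/(m − 1): 0.058 at m = 5 and 0.078 at m = 4.

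**The case against.** **The random effects are not spelled out.** The article names a hierarchical mixed model and lists no random effects, not even one for participant, and the quoted sentence concerns fixed effects. An unseen analysis plan could include a group level. This stands to the extent that a reader might infer that the protocol declares participants independent; it does not say so. What remains is that the article goes as far as naming the model, its effects, the test and the only nesting, and group delivery is reflected in none of them.

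**The inflation is conditional.** A reader might take it as established that type I error exceeds 5%. The documents give no ICC, and at 0.01 the excess is about half a percentage point. The primary time point is two months after the groups end, so a group effect must also persist that long. This stands, and the figures are therefore a range under assumption.

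**The percentages are not for the planned contrast.** They are exact only for a single-time comparison. Step 3 shows that the inflation for change from baseline can be smaller or larger, depending on r. This also stands.

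**The trial is not underpowered on this account.** A reader might infer from the missing design effect that 90 per arm is too few, or that the sample size itself raises type I error. Neither follows. The stated inputs need only 73–74 per arm, so 90 keeps 0.95 power up to an ICC of about 0.06–0.08, and the sample-size calculation does not affect the test's error rate. Equally, the protocol does not say that the surplus is meant for clustering, and extra participants in groups of the same size do not correct the standard error.

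**Facilitator effects may partly cancel.** Facilitators are trained in both interventions and may run groups in both arms. This makes facilitator a secondary concern; the therapy group is the main unit, because each group belongs to one arm.

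**Conclusion.** The concern holds in conditional form. As described, the primary analysis has no term for a dependence that group delivery can create. For any positive within-group correlation at 2 months, the standard error of the condition contrast is understated: by a factor of 1.07–1.10 at ICC 0.05 and 1.14–1.18 at ICC 0.10 for a T2 comparison. Actual type I error is then about 7% and 9–10%, and close to nominal (about 5.5%) at ICC 0.01.

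This rests on an assumed ICC, on SC groups being similar in size to CWC groups and, for the change contrast, on an unknown baseline-to-T2 correlation. The sample size is adequate for modest clustering; the valid criticism there is that no allowance is stated and that 90 does not follow from the inputs. The power figures assume 90 analysed per arm, that is, 200 enrolled. The abstract gives 90 per arm as randomised; 10% attrition from that would leave 81 analysed per arm, with power 0.936–0.945 at ICC 0.05.

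**What to change.** **Analysis.** State a therapy-group random effect that acts on the post-baseline visits (group-by-visit). Alternatively, fit a baseline-adjusted model for the 2-month outcome with a group random intercept. Use small-sample degrees of freedom such as Satterthwaite, given about 18–22 groups per arm. Do not rely on a time-constant group intercept alone. Consider a facilitator effect where one facilitator runs several groups, as a secondary matter.

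**Data.** Keep the group ID, and the facilitator ID if that effect is used, in the analysis dataset.

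**Sample size.** Restate the basis with the group size in both arms, an ICC range and the resulting design effect. Give power for 90 analysed per arm: about 98% without clustering, 96% at ICC 0.05 and 93% at ICC 0.10. No extra enrolment beyond 200 is needed, provided power slightly below 0.95 is accepted at the upper end of that range.

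**Cost.** Wording in the analysis plan, one or two identifier variables, and intervals about 8–16% wider at ICC 0.05–0.10 (√1.175 = 1.08, √1.35 = 1.16, for m = 4.5).

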**Methods:**

A single-blind, parallel, randomized controlled trial will be carried out via video conferencing in a small group format. Following informed consent, adults that screen positive for levels of psychological distress (Kessler 10 (K-10 score ≥ 20) and have access to a videoconferencing platform will be randomised to an adapted version of CWC (*n* = 90) or Supportive Counselling (SC) (*n* = 90). The primary outcome will be reduction in psychological distress including anxiety and depression at 2-months post treatment. Secondary outcomes include worry, positive wellbeing, and stress in relation to COVID-19.

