## Methods

### Aims & hypotheses

This study will assess the effectiveness of an adapted version of CWC to specifically target mental distress arising from the COVID pandemic in a cohort of university students in India. The randomized controlled trial (RCT) will compare CWC with Supportive Counselling (SC) in participants reporting moderate to severe psychological distress in a group format. The primary hypothesis is that those receiving group CWC will report lower psychological distress compared to those who received supportive counselling. To this end, we hypothesize that the impact of social support and alliance afforded by the supportive counselling condition will not exceed the therapeutic effects of evidence-based skills covered in CWC. The primary outcome measures are anxiety and depression, as measured by the Hospital Anxiety and Depression Scale (HADS, [21] subscales.

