### Primary outcome

The primary outcome will be severity of anxiety and depression symptoms as measured using the Hospital Anxiety and Depression Scales (HADS) [25]. The HADS is a 14-item scale consisting of two sub-scales: HADS-A (Anxiety, 7 items, range 0–21) and HADS-D (Depression, 7 items, range 0–21). Higher scores indicate more severe anxiety and/or depression. The minimal clinically important difference (as based on the effect size approach) has been determined at 1.32 for HADS-A and 1.40 for HADS-D and 1.17 for the HADS total score [26].

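### The planned 2-month contrast leaves baseline HADS free to differ between arms instead of adjusting for it, which costs some precision; the endpoint wording should be settled in the same edit

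*Protocol article*

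**What the plan says.** - **Model.** Design & setting describes two conditions by four assessment points, T0 included. Statistical analysis lists terms for time, condition and their interaction, and plans Wald tests for the time and condition effects. The target is the between-arm difference in change over time, "with the main outcome time point being the 2-month follow-up, relative to baseline". No baseline covariate and no common baseline mean is mentioned.
- **Order of events.** Randomization states that allocation follows completion of the T0 assessment.
- **Endpoint in level wording.** Aims & hypotheses predicts that "those receiving group CWC will report lower psychological distress compared to those who received supportive counselling". The Primary outcome section says "The primary outcome will be severity of anxiety and depression symptoms".
- **Endpoint in change wording.** The abstract's Methods paragraph says "The primary outcome will be reduction in psychological distress including anxiety and depression at 2-months post treatment", and Statistical analysis compares T2 with baseline.
- **Sample size.** The calculation is "based on a two-group comparison of the primary outcome at the 2-month follow-up timepoint", with an effect size of 0.6, 90 per arm, power 0.95 and two-sided alpha 0.05. The text says neither score nor change, and does not say which SD the 0.6 is measured in.

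**The concern.** Because T0 comes before allocation, both arms have the same expected T0 mean, and any observed T0 difference is chance. A model that lets the arms differ at T0 and then tests T2 against T0 subtracts that chance difference in full. An efficient analysis subtracts it only as far as T0 predicts T2. The plan would thus give up precision that data already collected from every participant could supply.

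The endpoint wording adds a smaller problem. A reader cannot tell from the article whether the effect size of 0.6 is in SDs of the T2 score or of the change, so the stated power cannot be tied to the contrast that will be tested.

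**Working it through.** **Inputs from the protocol.** Effect size 0.6, two-sided alpha 0.05, power 0.95, 90 per arm, 10% attrition and 200 enrolled (Sample size); four occasions and the model terms (Design & setting, Statistical analysis); T0 before allocation (Randomization).

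**Assumptions.** r = 0.3, 0.5 and 0.7, since the protocol gives none; equal SDs at T0 and T2, set to 1; the 0.6 read in SDs of the T2 score; categorical time; complete data on 90 per arm; no clustering by therapy group.

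**The plan's own figure.** An effect of 0.6 at power 0.95 and two-sided 0.05 needs 73 per arm by the normal approximation, or 74 by the t-test, not 90. Ninety per arm matches an effect of about 0.54; at 0.6 it gives power 0.981 for an unadjusted T2 comparison. The attrition step does reproduce: 180/(1 − 0.10) = 200. The mismatch between 73 and 90 is a separate matter. Below, 90 per arm and 0.6 are taken as given.

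**Variance per participant, with T2 score variance = 1**
- Unadjusted T2 score: 1
- Change from T0: 1 + 1 − 2r = 2(1 − r)
- T2 adjusted for T0: 1 − r²
- Ratio of change to adjusted: 2(1 − r)/(1 − r²) = 2/(1 + r), which exceeds 1 for every r below 1

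**Standard errors**, SE = √(2 × variance/90). Generalised least squares for the four-visit model (exchangeable covariance) gave exactly the change-score SE when T0 means were free, and exactly the adjusted SE when they were constrained to be equal.

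| r | T2 score | Free T0 means (change) | Common T0 mean (adjusted) | SE ratio √(2/(1+r)) | Sample equivalent (1+r)/2 |
|---|---|---|---|---|---|
| 0.3 | 0.149 | 0.176 | 0.142 | 1.240 | 0.65 |
| 0.5 | 0.149 | 0.149 | 0.129 | 1.155 | 0.75 |
| 0.7 | 0.149 | 0.115 | 0.106 | 1.085 | 0.85 |

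**Power**, Φ(d/SE − 1.96). Example at d = 0.6, r = 0.3: 0.6/0.1764 − 1.96 = 1.44, so 0.925. The d = 0.4 columns are illustrative; that value is not in the protocol.

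| r | d = 0.6, change | d = 0.6, adjusted | d = 0.4, change | d = 0.4, adjusted |
|---|---|---|---|---|
| 0.3 | 0.925 | 0.988 | 0.621 | 0.803 |
| 0.5 | 0.981 | 0.996 | 0.765 | 0.873 |
| 0.7 | 0.999 | 1.000 | 0.934 | 0.964 |

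At d = 0.6 the change contrast stays at or above 0.95 for r of about 0.4 or more (0.957 at r = 0.4) and falls to 0.889 at r = 0.2.

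**Unequal SDs.** Screening on the K-10 may narrow the T0 spread. Let the T0 SD be s times the T2 SD. The change variance is s² + 1 − 2rs, and it exceeds the adjusted variance 1 − r² by (s − r)². The change contrast is thus never more precise, and equals the adjusted one only when r = s. For example, with s = 0.7 (an assumption) and r = 0.3, change is 0.49 + 1 − 0.42 = 1.07 and adjusted is 0.91. The SE ratio is √(1.07/0.91) = 1.084, an excess of about 8% instead of 24%.

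**The case against.** The strongest reply is that nothing here is invalid. Under randomisation the interaction contrast estimates the same treatment effect and keeps its type I error, so what remains is a choice between a sound analysis and a more efficient one. That is correct, and it limits the weight of the point.

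A second reply is that the article condenses the model and an analysis plan may add baseline adjustment. This stands in part. However, the article is not silent: it names the model terms, a tested condition effect, four occasions including T0, and a contrast against baseline. Together these describe free T0 means.

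Third, the equivalence with change scores needs categorical time and complete data, whereas the article speaks of linear time effects and expects about 10% attrition. The figures therefore measure the cost of leaving T0 unadjusted; they do not predict the exact output of the model as written.

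A reader might also infer more than the text supports:
- *That the score was powered but the change will be tested.* Sample size says neither; it refers only to the primary outcome at 2 months. The defect is that the scale is unstated.
- *That two rival primary tests inflate the false-positive rate.* Statistical analysis plans one. The level wording elsewhere introduces an instrument and states a hypothesis in plain terms; it sets up no second test.
- *That the mixed wording causes the loss of precision.* The loss comes from the model and would remain if every section said change.
- *That K-10 screening lowers r and so makes matters worse.* No document figure supports this, and a narrower T0 spread also shrinks the change-score variance, as shown above.
- *That the change contrast is worse than a plain T2 comparison.* Under equal SDs that holds only for r below 0.5.

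**Conclusion.** The point holds as one of efficiency and clarity. The model described leaves T0 means free although T0 precedes allocation. Under equal SDs, categorical time, complete data and no clustering, this raises the standard error of the T2 contrast by 24%, 15% and 8.5% at r = 0.3, 0.5 and 0.7, and possibly by less if screening narrows the T0 spread. At the planned 0.6 the drop in power is 0.063 at r = 0.3 (0.988 − 0.925), 0.015 at r = 0.5 (0.996 − 0.981) and negligible at r = 0.7. It is larger if the true effect is smaller: at 0.4 and r = 0.3 it is 0.182 (0.803 − 0.621). A smaller effect is conceivable, since the comparator is active whereas the Background says earlier trials of the parent intervention used usual care.

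The secondary point also holds: the endpoint is worded as a level in two places and as a change in two others, and the SD behind the 0.6 is not given. Neither point makes the planned test biased or invalid.

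**What to change.** Define the primary contrast once and use the same definition in the abstract, Aims & hypotheses, Primary outcome, Sample size and Statistical analysis: the CWC-minus-SC difference in HADS at T2, adjusted for T0 HADS. In the mixed model this can be done in either of two ways:
- keep T0 as an outcome occasion but give both arms a common T0 mean, with condition terms only at T1, T2 and T3; or
- model T1 to T3 with T0 HADS as a covariate, allowed to differ by visit.

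Name the T2 term as the primary test. Treat GAD-7, CSS, SIDAS and WHO-5 in the same way, each with its own T0 value. In Sample size, state which SD the 0.6 refers to. If it is the SD of the T2 score and the calculation ignored baseline, say so; the calculation is then conservative with respect to baseline adjustment, since 1 − r² is never above 1.

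The cost is some rewording and one changed model term. No new data, visits or participants are needed, because the T0 measures are already collected before allocation.
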